## 4. Outcomes measure

### 4.1. Primary outcomes

Changes of glycemia levels during 4-week perioperative period: mean glucose level during pre- and postoperative period, 24-hour glucose level amplitude, time of both higher and lower glucose level than average for the day in total, number of periods of both higher and lower than average glycemia levels for the day and its’ duration, number of days with higher mean glucose level than the mean for the corresponding pre- and postoperative period;Any cardiovascular events during follow-up (heart stroke, brain stroke, coronary arteries disease, transient ischemic attack;Any surgical site and/or implant complications during follow-up.

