## Abstract

In every surgical subspecialty surgical site infection (SSI) or implant infections, although occur seldom, pose a threat to patients’ health. Risk factors of such states is diabetes mellitus (DM), considered one of the most widespread health-related problems of the 21st century. Orthopedists perform big joint replacements that usually concern older adults and therefore often deal with patients suffering from comorbidities. DM is frequently one of them and can furthermore often remain underdiagnosed. The other risk for complication is a rapid beginning of the rehabilitation which starts on the day following the surgery. To eliminate the debilitating impact of DM and hypoglycemia on surgical patients, we aim to investigate the relationship between the glycemia values and the postoperative outcomes in certain periods of time in patients undergoing orthopedic surgeries. Participants meeting inclusion criteria will have inserted a glycemia measuring device (Dexcom G5, Inc., San Diego, CA) in the periods of time. First time it will take place 14 days prior to the surgery and right after the surgery for the second time for the period of another 14 days. All patients will undergo standard total knee arthroplasty or total hip arthroplasty procedures. Patients will be assessed preoperatively and 14 days, 1, 3, 6, 12, and 24 months postoperatively. The assessment of the joint condition will consist of: patient-reported outcomes (The Knee injury and Osteoarthritis Outcome Score, Harris Hip Score, the Western Ontario and McMaster Universities Osteoarthritis Index [WOMAC]); assessment of potential SSI and cardiovascular complications (the Finnish Diabetes Risk Score [FINDRISC], the Systematic Coronary Risk Evaluation [SCORE]) and the clinical examination. To investigate the influence of orthopedic surgery (anesthesia) on glycemia and the significance and safety of early patients mobilization after the big joints surgeries. To investigate changes of glycemia in patients with normal glycemia metabolism, potentially protecting them from hypoglycemia during hospital stay and increasing their awareness of potential development of DM in the future. Additionally, this study will correlate perioperative glycemic levels with risk of cardiovascular events in one year follow-up, and its influence on SSI and implant complications.

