## 2. Materials and Methods

Patients for this prospective observational study will be recruited among those qualified for elective TKA or THA at the Department of Orthopaedics and Rehabilitation in academic Miedzyleski Specialist Hospital in Warsaw. 100 patients will be included. Every patient will be evaluated with the use of Finnish Diabetes Risk Score (FINDRISC), which allows for evaluation of risk of developing DM in 10 year time in patients who were not previously diagnosed^[25–27]^ and SCORE scale, which allows for evaluation of risk of death in 10 years due to cardiovascular events.^[28–31]^ To perform this evaluation data such as sex, age, body mass index (kg/m^2^), and waist circumference (cm) will be measured. Also, data such as physical activity, diet, used medications, smoking, and family history will be collected. Prior to the surgery every patient will undergo a blood withdrawal, which is routinely performed for every patient qualified for the orthopedic surgery. This blood sample analysis will include glycemia level, HbA1c, morphology, renal function parameters, lipidogram, level of C-reactive protein, and urine test. What is more, every patient will fulfill a questionnaire regarding functioning of the joint affected by OA. The scales used will be The Knee injury and Osteoarthritis Outcome Score scale (Knee injury and Osteoarthritis Outcome Score)^[32]^ or Harris Hip Score (HHS) scale^[33]^ according to the affected joint. Both scales contain questions about patients’ everyday life and limb function.

Inclusion criteria consist of willingness to participate in the study, being qualified for TKA or THA due to the primary OA and age >18 years.

Exclusion criteria consist of lack of acceptance to participate in the study, being qualified for nonsurgical treatment, other diseases but DM, compensated thyroid disorders and hypertension, poorly controlled DM and/or poorly controlled hypertension, patients with diabetes mellitus type 1, patients from the rest homes, pregnant women, patients who underwent lower limb surgeries recently, patients who in opinion of the research team might be poorly compliant, poor Polish language fluency.

Patients will have a glycemia measuring device (Dexcom G5, Inc., San Diego, CA) implemented twice. First time 14 days prior to the surgery, second time after the surgery and will keep wearing it for 14 days.

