All patients will undergo TKA and THA procedures with standard perioperative antibiotics prophylaxis with use of 3 doses of 750 mg of cefuroxime–preoperatively, 6 and 12 hours postoperatively, and standard thrombosis prophylaxis of one dose of 40 mg low-molecular weight heparin. In every case posterior-stabilized total knee prosthesis (PERSONA, Zimmer Biomet, Warsaw, IN) or long-stem cementless Polarstem R3 total hip prosthesis (Smith & Nephew, Baar, Switzerland) will be used. Every participant will be rehabilitated immediately after the surgery with full weight bearing walking in the first 24 hours postoperatively, with the discharge from the hospital on the third day postoperatively.

During standard control visit, 14 days after the surgery skin sutures will be removed and the glycemia measuring device will be taken out. The measurements from the whole period of treatment will be collected from the device. Patients will be controlled during the planned visits 3, 6, 12, and 24 months after the surgery. In case of hyperglycemic event at any time of hospital stay or follow-up, patients will be referred to the internal medicine unit and remain controlled by the physicians according to the glycemic control guidelines.

During every visit glycemia level will be measured from standard blood samples, objective functional outcome will be assessed and radiological standard imaging of the operated limb will be performed. History of any cardiovascular event and/or surgical SSI will be noted.

The presenting study meets STrengthening the Reporting of OBservational studies in Epidemiology guidelines for ensuring high-quality presentation of the conducted prospective observational study.

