## 3. Ethics, data management, and statistical analysis

All procedures used for this study have been approved by the Institutional Bioethics Committee of the Medical University of Warsaw (number of approval: KB/104/2020). The study was registered in the ClinicalTrials.gov database (NCT04484480). All patients will be obliged to give written consent for their participation in the study. Collected data will be stored at the Department in a database created particularly for this study and secured appropriately. In the database each participant will have a special code to minimize the risk of identification of a particular patient. Only patients who attend all visits, fill in all questionnaires and do not interrupt the course of the study in any other way will be included in the analysis. The consequence of the absence on a control visit will be exclusion from the study.

Power analysis was performed to assess how many patients should be included in the study. Determining effect size was hindered by lack of literature comparing mean values and standard deviations (SD) between groups with and without complications. The effect size can be deemed “large,” described numerically as 0.8 by Cohen. However, we decided to be more conservative and used an effect size of 0.6, located between “medium” and “large” in Cohen scale. Standard *P* value of .05, beta value of 0.8, and allocation ratio of 1/1 were used, resulting in a total needed sample size of 90 patients. Taking into consideration that 10% of patients might drop off the follow-up predicted number of participants is 100.

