Basic analysis will include descriptive statistics of demographic characteristics to assess both groups homogeneity. Such analysis will be done several times during testing to detect any confounders that could impact the results. Continuous variables will be summarized with number of cases, means, standard deviations, medians, ranges, and first and third quartile (Q1 and Q3). All comparisons will be performed between continuous variables in paired groups, therefore either a 2-sided Student *t* test for paired groups or Wilcoxon Signed Rank test will be used. Distribution normality will be examined using the Shapiro–Wilk test. An overall alpha-level of 0.05 will be used as a cut-point for statistical significance and all statistical tests will be 2-sided. Significance level will be set at *P* value below .05. Outliers will be initially identified using interquartile range (IQR) as observations with values above Q3-1.5IQR or below Q1-1.5IQR and will be examined individually. All data will be presented with extreme and outlier observations or committed with appropriate annotation.

All statistical analyses will be conducted using SAS 9.4 for Windows (SAS Institute Inc., NC).

The study protocol was published before the start of the study on clinicaltrials.gov. The results of the study will be published in (inter-)national scientific journals and guidelines. The data that support the findings of this study will be available from the corresponding author - OA, upon reasonable request.

Data reported in the presenting study will be prospective observational data. The treatment will be reliable to the patients’ condition. And the procedure of implementing the glucose measuring device will be the same throughout the whole cohort. This has to be kept in mind for the interpretation of the results.

The inclusion and exclusion criteria presize how the authors deal with the risk of bias such as severity of illness or presence of comorbidities on intervention group assignment.

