Results of the presenting paper will allow us to investigate the influence of orthopedic surgery on glycemia and possible modifications of hyperglycemia treatment in perioperative period in patients with T2DM or glucose intolerance. What is more, it will allow for investigation of changes of glycemia in patients with normal glycemia metabolism, potentially protecting them from hypoglycemia during hospital stay and increasing their awareness of potential development of DM in the future. Additionally, this study will correlate perioperative glycemic levels with risk of cardiovascular events in 1-year follow-up, and its influence on SSI and implant complications. Thanks to these findings surgeons will be able to lower the risk of such complications in the future, hence lowering mortality and increase the quality of life, especially in patients with DM and in those with high risk for developing this disorder. Another advantage of this study is the fact that it contains patients without recognized DM and without carbohydrate metabolism disorders and assesses their glycemia fluctuations. Such knowledge might help in development of an algorithm for perioperative care with stress on glucose level control as it is a period when patients are exposed to significant glycemia fluctuations. What is more, it must be emphasized that this study has a unique model, in which glycemia monitoring will involve both pre- and postoperative period for every included patient. Such a way of analyzing patients allows one to form a well visualizing control group, because every measurement after the surgery has its counterpart before the surgery. However this study did not exclude the disadvantages. Patients before the surgery and after hospital discharge will not be monitored all the time. Therefore, we must take into consideration the possible patients’ interference with glycemia levels in opposition to recommendations. That may lead to obtaining invalid results and risk of bias.

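### The only primary measure of glucose level averages 14 postoperative days, so a change confined to the roughly 3-day hospital stay would show at about one fifth of its size; add a hospital-stay contrast.

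*Protocol article*

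**What the plan says.** Section 4.1 of the Protocol article opens the primary outcomes with "Changes of glycemia levels during 4-week perioperative period: mean glucose level during pre- and postoperative period". It then lists, under the same outcome, the 24-hour amplitude, the time and the number of periods above or below the day's average, and the number of days whose mean exceeds the mean of the corresponding period.

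Section 2 gives the sensor timing as "First time 14 days prior to the surgery, second time after the surgery", with 14 days of wear, and describes the stay as ending "with the discharge from the hospital on the third day postoperatively". Section 1 gives a median stay of 3 days.

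The aims include, in the Abstract, "To investigate the influence of orthopedic surgery (anesthesia) on glycemia" and the safety of early mobilisation. Section 6 speaks of studying patients with normal glucose metabolism, "potentially protecting them from hypoglycemia during hospital stay", and says that the glycaemic profile during the stay needs evaluation. Section 6 also presents monitoring of the whole period before and after surgery as the study's distinctive feature.

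**The concern.** Several aims concern events of the first three days: the operation, the first full-weight-bearing walk within 24 hours, and hypoglycaemia on the ward. The period mean gives those days about 3/14 of the weight and gives the other 11 days, spent at home, the rest. Section 6 itself warns that patients are not monitored all the time at home and may affect their own glucose there.

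The other primary glucose measures do not fill the gap. Time and periods above or below average take the day's own average as reference, so a shift lasting the whole day moves the reference with it. The count of high days is referenced to its own period's mean, which the same shift also raises. The amplitude measures spread, not level.

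At stake is the reading of a null result. A real change in hospital could be averaged down, or offset by an opposite change at home, and a flat 14-day contrast could then be taken as no effect of surgery.

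**Working it through.** **The article's own figure.** Section 3 uses "we decided to be more conservative and used an effect size of 0.6" with "beta value of 0.8, and allocation ratio of 1/1 were used, resulting in a total needed sample size of 90 patients". For two independent means, two-sided 0.05, the exact t calculation gives 45 per group (power 0.804), total 90. Then 90/0.90 = 100. The figure reproduces, but it is for patients with versus without complications. No power is stated for the paired glucose contrast, so the 90 completers are used below only as the number of pairs.

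**Inputs.** From the article: 14 postoperative sensor days, a stay of about 3 days, a paired test, and "An overall alpha-level of 0.05 will be used as a cut-point for statistical significance and all statistical tests will be 2-sided". Assumed, because the article gives no SD, effect size or duration for this contrast: the standardised paired change d over the 3 days (0.3 to 1.0), the noise structure, and the fraction g of the excursion that persists over days 4 to 14.

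**Dilution of the mean.** The share of the 3-day shift kept in the 14-day mean is f = (3 + 11g)/14.
- g = 0: 3/14 = 0.214. A 30 mg/dL rise over 3 days (illustrative) becomes 6.4 mg/dL.
- g = 0.25: 5.75/14 = 0.411.
- g = 0.5: 8.5/14 = 0.607.
- If the stay is counted as four calendar days with g = 0: 4/14 = 0.286.

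**Noise.** The benchmark is the 3-day postoperative mean against the 14-day preoperative mean.
- *Same SD of change in both windows:* the standardised effect on the 14-day mean is d × f.
- *Independent daily noise:* the variance of the change is proportional to 1/3 + 1/14 for the 3-day window and to 1/14 + 1/14 for the 14-day window. The SD ratio is √(0.4048/0.1429) = 1.683, so the effect is d × f × 1.683. At g = 0 the share kept is 0.214 × 1.683 = 0.361.

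**Power.** Paired t test, 90 pairs, two-sided 0.05, noncentrality = effect × √90:

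| d over 3 days | g | Power, 3-day mean | Power, 14-day mean, same SD | Power, 14-day mean, independent noise |
|---|---|---|---|---|
| 0.3 | 0 | 0.80 | 0.09 | 0.17 |
| 0.5 | 0 | 0.997 | 0.17 | 0.40 |
| 0.6 | 0 | >0.999 | 0.23 | 0.53 |
| 1.0 | 0 | >0.999 | 0.52 | 0.92 |
| 0.5 | 0.25 | 0.997 | 0.49 | 0.90 |
| 0.5 | 0.5 | 0.997 | 0.81 | 0.998 |
| 0.3 | 0.5 | 0.80 | 0.40 | 0.82 |

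With four hospital days, d = 0.5 and g = 0, the 14-day power is 0.27 (same SD) to 0.52 (independent noise).

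**Check on the count of high days.** A 30 mg/dL rise was simulated on 3 of 14 days, with independent normal daily means and SD 5 to 20 mg/dL (assumed). The average number of days above the period's own mean fell from 7.0 to between 4.0 (SD 5) and 6.7 (SD 20). This measure can therefore move opposite to the true change in level.

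**The case against.** The strongest reply is that the hospital stay is only one of the targets. Section 1 names the lack of continuous measurements before and after hospitalisation as the gap, section 4.1 sets a 4-week window, and section 6 wants to relate perioperative glycaemia to later cardiovascular events, infection and implant complications. For those aims the days at home are part of the estimand. This stands. It is the reason to keep the 14-day mean and not to demote a primary measure of a registered study.

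A second reply is that the mean is one of several co-listed measures, some of them defined by day, and that section 6 says each postoperative reading has a preoperative match, which would permit day-level contrasts. The design does permit them. But the listed day-level measures are a spread or are self-referenced, and none is a level contrast over the stay.

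A third reply is that a journal article leaves window details to a fuller plan. That is fair for detail, and if such a plan already splits the period, the point is met. Here, however, the published outcome itself states the averaging period.

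Two stronger readings are tempting. One is that the 14-day mean removes most of the power as a matter of fact. The documents do not support this: they give no SD, do not say that the excursion ends at discharge, and claim no power for this contrast. With half the excursion persisting and independent daily noise, power at d = 0.3 is 0.82 on the 14-day mean against 0.80 on the 3-day mean. The other is that the day of surgery falls in neither sensor window. The article does not say so. The Abstract places the second sensor right after surgery, so later readings that day can belong to the postoperative period, and removal of the first sensor is not described.

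**Conclusion.** The concern holds as a mismatch between several stated aims and the averaging window of the only primary measure of glucose level. The dilution to 21% (29% if four days are counted) is plain arithmetic for an excursion confined to the stay.

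The power loss is conditional. With 90 pairs, d = 0.5 and no persistence, power falls from over 99% to between 17% and 40%. With a quarter persisting it is 49% to 90%, and with a half 81% to over 99%. All of this rests on assumed effect sizes, noise and duration.

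The claim about anaesthesia is also conditional: it needs sensor readings that cover the operation, and the article does not establish that there will be any. The point merits a change because the data will already be collected, but it does not invalidate the 14-day mean.

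**What to change.** In section 4.1, keep the 14-day mean and add a prespecified paired contrast: mean glucose from insertion of the second sensor to discharge, against the patient's preoperative mean. Report discharge to day 14 against the same preoperative mean as a separate contrast.

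State that postoperative readings on the day of surgery belong to the hospital-stay window, so that no reading falls in two windows. If no sensor reading covers the operation itself, word the conclusion as postoperative glycaemia and not as an effect of anaesthesia.

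No new patients or measurements are needed, only outcome wording and some programming. The price is one or two more comparisons, whose place among the outcomes should be stated, and a 3-day mean that is noisier per patient than a 14-day mean: 1.68 times the SD of change if daily noise is independent.

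### Section 4.1 counts coronary artery disease, a chronic condition, as a primary cardiovascular event, and its detection may differ by glucose level because hyperglycaemia triggers referral to physicians

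*Protocol article*

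**What the plan says.** Section 4.1 of the protocol article defines the second primary outcome as "Any cardiovascular events during follow-up (heart stroke, brain stroke, coronary arteries disease, transient ischemic attack". Nothing in the article limits the coronary item to acute presentations.

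Section 2 sets how these outcomes come to light:

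- Entry excludes patients with "other diseases but DM, compensated thyroid disorders and hypertension" as the permitted exceptions, so known coronary disease appears to be excluded.
- Baseline assessment consists of blood and urine tests, joint questionnaires, FINDRISC and SCORE. At follow-up visits there is a glucose measurement, a functional assessment and imaging of the operated limb. No cardiac testing is described at either stage.
- For everyone, "History of any cardiovascular event and/or surgical SSI will be noted" at the visits, which run to 24 months.
- "In case of hyperglycemic event at any time of hospital stay or follow-up, patients will be referred to the internal medicine unit", and they then "remain controlled by the physicians according to the glycemic control guidelines".

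The Abstract and section 6 state the planned use of the outcome: "this study will correlate perioperative glycemic levels with risk of cardiovascular events in 1-year follow-up". Section 4.2 adds a secondary correlation of FINDRISC with cardiovascular events.

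**The concern.** An infarction, a stroke or a transient ischaemic attack has a date of onset. Stable coronary artery disease has a date of diagnosis, which depends on when somebody looked. With known disease apparently excluded and no baseline test for silent disease, a coronary case counted during follow-up is a first diagnosis. It may have been present before surgery, and so before the postoperative glucose with which it is to be correlated.

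The exposure also affects the chance of being looked at. A hyperglycaemic event brings continuing contact with internal medicine physicians, and the article describes no counterpart for other patients. If that contact leads to more coronary diagnoses, glucose and the outcome will be associated without any effect of glucose. Section 6 expects the findings to help surgeons lower the risk of complications, so a distorted estimate could be put to use.

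**Working it through.** **The plan's own figure.** The sample size reproduces. With a standardised effect of 0.6, two-sided alpha 0.05, power 0.8 (printed as beta) and 1:1 allocation, a two-sample t-test needs 44.6, so 45 per group and 90 in total. Allowing for 10% dropout, 90 / 0.90 = 100. This point does not alter that calculation; it only borrows the 90 and the 45 v 45 split.

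**Acute cardiac events.** Section 6 cites 0.2% to 0.8% for major cardiac complications. In 90 patients that is 90 × 0.002 = 0.18 to 90 × 0.008 = 0.72 events. The cited rate has no time window and does not cover stroke or transient ischaemic attack, so it is a floor for the acute part of the outcome and not an estimate of it. A higher rate of 2% (assumed) is therefore shown as well: 90 × 0.02 = 1.8 events.

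**Illustration with no true glucose effect.** Let h be the acute event rate and u the prevalence of undiagnosed coronary disease, both equal in the two groups. Let d1 and d0 be the probabilities that such disease is diagnosed in referred and non-referred patients. Then

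- p1 = h + (1 − h) × u × d1
- p0 = h + (1 − h) × u × d0
- spurious risk ratio = p1 / p0
- coronary share of counted events = 1 − 90h / (45p1 + 45p0)

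The values of u, d1, d0 and the 45 v 45 split by referral are assumptions; the documents give none of them. One line worked through (h = 0.2%, u = 20%, detection 50% v 10%):

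- p1 = 0.002 + 0.998 × 0.20 × 0.50 = 0.102
- p0 = 0.002 + 0.998 × 0.20 × 0.10 = 0.022
- ratio = 4.64

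| h | u | d1 v d0 | p1 v p0 | Risk ratio | Expected events per 45 | Coronary share | Fisher rejects |
|---|---|---|---|---|---|---|---|
| 0.2% | 20% | 20% v 20% | 4.2% v 4.2% | 1.00 | 1.9 v 1.9 | 95% | 0.4% |
| 0.8% | 5% | 40% v 20% | 2.8% v 1.8% | 1.55 | 1.3 v 0.8 | 65% | 0.1% |
| 0.2% | 20% | 40% v 20% | 8.2% v 4.2% | 1.95 | 3.7 v 1.9 | 97% | 3.4% |
| 0.8% | 5% | 50% v 10% | 3.3% v 1.3% | 2.53 | 1.5 v 0.6 | 65% | 0.2% |
| 0.2% | 20% | 50% v 10% | 10.2% v 2.2% | 4.64 | 4.6 v 1.0 | 97% | 15.0% |
| 2% (assumed) | 5% | 40% v 20% | 4.0% v 3.0% | 1.33 | 1.8 v 1.3 | 42% | 0.3% |
| 2% (assumed) | 20% | 50% v 10% | 11.8% v 4.0% | 2.98 | 5.3 v 1.8 | 75% | 14.2% |

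Three things follow. With equal detection the ratio is 1.00. With d1 above d0 it exceeds 1 whatever the other inputs; only its size changes. With the coronary item removed it returns to h / h = 1.00, because the model gives both groups the same acute rate.

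**The case against.** The strongest reply is that the detection mechanism is inferred. The referral is for glucose control, and no cardiac work-up is mentioned. The article does not say what other care non-referred patients receive, so a reader who infers that they are seen only by the orthopaedic clinic goes beyond the text. All patients have the same visits with the same history-taking, and the same baseline SCORE and lipids. This stands as a limit on certainty. It does not remove the problem: a history records only diagnoses that someone has already made, and equal history-taking does not equalise who was examined elsewhere.

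A second reply is that the coronary item may loosely mean coronary events, and that component criteria belong in a fuller document. But heart stroke is already listed separately, so the item appears to add non-acute disease. The component list itself is fixed in the article.

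Third, a correlation can describe a marker and need not claim that a few weeks of glucose cause coronary disease. That is fair, but unequal detection distorts a marker association too.

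Fourth, the illustrative ratios are produced by their assumed inputs. This stands in full. It also stands that the cited cardiac rate is a poor benchmark for an outcome that includes stroke and transient ischaemic attack. At an acute rate of 2% the coronary share can fall to 42% with unequal detection.

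**Conclusion.** The point holds as a possible bias in one primary outcome. The article counts a chronic condition as an event, ascertains it from history alone, and gives patients with the exposure of interest extra physician contact. Nothing in it restricts the item to acute presentations or equalises detection. The likely direction, assuming that physician contact raises detection, is to make hyperglycaemia look harmful. The FINDRISC correlation shares the outcome definition and so may also be affected.

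The size cannot be derived from the documents. Under the stated assumptions, the spurious ratio is 1.55 to 1.95 for 40% v 20% detection and about 2.5 to 4.6 for 50% v 10%, at the cited acute rates.

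A reader might infer three stronger claims that the documents do not support:

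- **The study is headed for a false positive.** Rejection by Fisher's test reaches only about 15% in the least favourable case. Section 3 describes only paired comparisons of continuous variables and no test of this binary outcome. The harm is a distorted estimate.
- **Coronary disease will dominate the composite.** This depends on the assumed prevalence and on an acute rate that the documents do not give for the whole outcome.
- **Counted cases will mostly predate surgery.** They may, but no figure in the article settles it.

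The mean glucose and surgical-site outcomes are unaffected.

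**What to change.** In section 4.1, replace the coronary artery disease item with acute coronary events with onset after surgery, and say how this relates to the heart stroke item so that the two do not overlap. Use the revised outcome for the glucose correlation. Report new diagnoses of stable coronary disease separately and descriptively, and add a sensitivity analysis that includes them. The FINDRISC correlation in section 4.2 should refer to the same revised definition.

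The change is to wording and reporting. History is already noted at the visits, so no extra visits, patients or tests are needed, and the referral arrangement is untouched.

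The cost is fewer counted events, possibly substantially fewer: at the cited rate, 0.18 to 0.72 acute cardiac events in 90 patients, before any strokes or transient ischaemic attacks. The cardiovascular association should therefore be presented as descriptive. Acute events are less open to unequal detection than stable disease, though not wholly immune, so the change reduces the bias and does not guarantee its absence.
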